## Abstract

**Background:**

Breast cancer is the leading cause of global cancer incidence. In early-stage disease, standard treatment with breast-conserving surgery followed by whole breast irradiation (WBI) is associated with excellent outcomes. Multiple studies with extensive follow-up periods have demonstrated the comparative efficacy and toxicity outcomes of partial breast irradiation (PBI) in contrast to WBI. Various dose fractionation schedules for PBI have been recommended in clinical practice guidelines. In British Columbia (BC), a dose of 26 Gy in 5 fractions has been adopted. Early studies on single-fraction (SF) radiation for PBI have investigated its safety and effect on cosmetic outcomes, with promising initial results. In the context of the ongoing health care crisis, single-fraction PBI has the potential to reduce wait times and improve access to radiation. This study will therefore investigate a single-fraction PBI dose of 13 Gy.

**Methods:**

This is a phase II randomized controlled trial, with a primary objective of testing the feasibility of randomizing participants to 1 vs. 5 fractions of PBI for early stage, node negative, breast cancer. The primary endpoint is the ability to accrue 60 participants at 4 of the 6 BC Cancer centres over a 2- year period and to randomize them to 1 vs. 5 fractions of radiotherapy for PBI. Its secondary endpoints are time from CT simulation to partial breast radiotherapy, local control rates, quality of life as measured by Prospective Outcomes and Support Initiative (POSI)-Breast, rates of provider-rated toxicities as measured by Common Terminology Criteria for Adverse Events (CTCAE), rates of participant-reported toxicities as measured by participant reported outcome version of CTCAE (PRO-CTCAE), overall survival, and progression-free survival.

**Discussion:**

One of the trial’s objectives is testing the feasibility of randomizing participants to single vs. multiple fractions for PBI. If successful, it will lead to a phase III non-inferiority trial with the potential to inform breast cancer treatment guidelines. Ultimately, if found to be non-inferior, a single-fraction PBI can reduce wait times, facilitate access to radiation, and improve patient convenience, particularly for those in rural and remote communities who must travel long distances to receive high-quality cancer care.

**Trial registration:**

Clinicaltrials.gov identifier: NCT06885671. Date of Registration: 14 March 2025.

## Background

Breast cancer is the leading cause of global cancer incidence, with an estimated 2.3 million new cases being diagnosed worldwide in 2020 [1]. In high income countries, screening strategies result in detection of early-stage breast cancers resulting in a 5- year survival rate beyond 85% [2].

Standard treatment for early-stage breast cancer is surgery, oftentimes followed by adjuvant treatment such as radiotherapy and hormonal therapy. Prior to advancements made in the 1970s, the surgical approach to treating breast cancer relied heavily on the radical Halsted mastectomy. However, subsequent research revealed that employing breast-conserving surgery alongside radiotherapy yielded comparable outcomes to the Halsted mastectomy for tumors measuring up to 5 cm in size [3–5]. Thus, breast-conserving surgery followed by whole breast irradiation (WBI) became standard of care treatment for early-stage breast carcinoma with excellent local recurrence rates and breast cancer-specific mortality [6, 7]. 

Over the past few decades, partial breast irradiation (PBI) has emerged as an alternative to WBI. PBI is a targeted radiation approach commonly administered post-lumpectomy, specifically targeting the tumor bed. This targeted therapy reduces the exposure to other nearby tissues such as lungs, heart, and chest wall. PBI is delivered through several different techniques, including brachytherapy, intraoperative therapy with electrons or photons, and External Beam Radiotherapy (EBRT) using a Linear Accelerator (LINAC) machine [8]. 

The comparative efficacy and toxicity outcomes of PBI in contrast to WBI have been documented across numerous randomized trials with extensive follow-up periods. The 2017 IMPORT-LOW trial recruited 2018 early-stage breast cancer participants and split them between standard WBI with 40 Gy in 15 fractions, reduced dose WBI with 36 Gy in 15 fractions, and PBI with 40 Gy in 15 fractions. Five-year results confirmed that local relapse was minimal across all trial groups and that non-inferiority was shown for both partial-breast and reduced-dose radiotherapy [9]. In another trial comparing WBI to PBI done in Denmark, 865 participants were also treated with 40 Gy over 15 fraction doses. 10-year follow-up results confirmed that PBI for early breast cancer does not increase the risk of breast morbidity and recurrence [10]. The 2019 RAPID non-inferiority trial further enrolled 2135 participants and randomized them to either WBI or PBI. PBI was found to be non-inferior to WBI in preventing ipsilateral breast tumor recurrence (IBTR) in women [11]. These large, randomized control trials have validated the safety and efficacy of PBI, while updating the ASTRO guidelines to advise PBI for early breast cancer participants post-breast-conserving surgery (BCS) [8]. 

The initial conventional accepted radiation dose for WBI was 50 Gy in 25 fractions. In the early 2000s, the START-B trial showed that hypo fractionated WBI with 40 Gy in 15 fractions was not inferior to the conventional 50 Gy in 25 fractions, and guidelines were updated to include both [12]. The FAST-Forward Trial challenged this standard, by comparing the standard dosage of 40 Gy in 15 fractions to 27 Gy in 5 fractions, and 26 Gy in five fractions. The results show that 26 Gy in five fractions over 1 week is non-inferior to the standard of 40 Gy in 15 fractions over 3 weeks for local tumour control and is as safe in terms of normal tissue effects up to 5 years [13]. This has now become a standard dosage for practicing radiation oncologists [8]. 

Initial studies on single-fraction (SF) radiation for PBI have investigated its safety and effect on cosmetic outcomes. A phase I/II single arm prospective clinical trial has confirmed that a SF dose of 20 Gy of radiation delivered 2 to 8 weeks after lumpectomy is a well-tolerated therapy that does not adversely impact cosmesis or quality of life as reported by physicians and participants [14]. Another phase I trial has demonstrated that SF PBI can be employed to safely increase the dose up to 30 Gy in a SF with low toxicity and without detriment to baseline cosmesis [15]. Although longer follow-up would be needed to confirm efficacy results, initial tumor control data from these studies are promising.

Like other medical services in Canada impacted by the ongoing health care crisis, cancer radiation treatment wait-lists are continually growing. This presents a systemic need for efficient and accessible treatments. Employing a single fraction for PBI is one promising radiation technique that could reduce wait times and improve access to radiation. Participants with early stage, node negative breast cancer will benefit from a shorter course of radiotherapy that will save them time and money. The regimen will also be particularly advantageous for participants from rural and remote communities, who must travel long distances to receive high quality cancer care. This phase II trial of SF PBI vs. multiple fraction PBI is therefore proposed.

The standard arm will use a dose of 26 Gy in 5 fractions, which has been adopted in the province for PBI. This dose fractionation is based on data from the FAST-Forward trial and extrapolation of its results alongside the findings of IMPORT-Low, a partial breast radiation trial that used 40 Gy in 15 fractions [9, 13, 16]. 

In the experimental arm, this study will investigate a single-fraction PBI dose of 13 Gy. A similar single-fraction dose has been used in CT-guided high-dose-rate brachytherapy for breast intraoperative radiation therapy. A phase I trial by Showalter et al. [17] and its subsequent phase II trial [18] both utilized 12.5 Gy, a dose that was found to be feasible and safe.

A meta-analysis of the START pilot and START-A trials, which investigated hypofractionation in breast radiation, estimated an α/β value of 3.5 Gy for locoregional relapse [19]. Findings from the FAST-Forward trial showed a similar α/β value for tumor control, at 3.7 Gy [13]. Using the linear quadratic model, a dose of 26 Gy in 5 fractions is equivalent to 41.13 Gy in 2-Gy Fractions (EQD2). A single fraction of 13 Gy is estimated to be iso-effective to the control dose, with an EQD2 of 39 Gy.

According to FAST-Forward data, α/β values for late normal tissue effects may be closer to 2 Gy than the 3 Gy estimated in previous studies [13]. Using an α/β value of 2, a course of 26 Gy in 5 fractions and a single-fraction of 13 Gy are estimated to have iso-effective EQD2 values of 46.8 Gy and 48.75, respectively.

## Methods

The objective of this phase II randomized controlled trial is to test the feasibility of randomizing participants to 1 vs. 5 fractions of partial breast irradiation (PBI) for early stage, node negative, breast cancer. It also aims to collect data on the time from CT simulation to partial breast radiotherapy, and to compare toxicity, local control, quality of life (QoL) as measured by POSI-Breast, health provider rated toxicity as measured by Common Terminology Criteria for Adverse Events (CTCAE), participant self-reported toxicity as measured by participant reported outcome version of CTCAE (PRO-CTCAE), overall survival (OS), and progression free survival (PFS), between the two arms.

### Primary endpoint

The primary endpoint of the study is the ability to accrue 60 participants at 4 of the 6 BC Cancer centres over a 2- year period and to randomize them to 1 vs. 5 fractions of radiotherapy for PBI. This will be measured by the number of participants accrued in each of the BC cancer centres over a 2-year period for randomization to 1 vs. 5 fractions of radiotherapy for PBI.

### Secondary Endpoint(s)

The secondary endpoints of the study are the following:

Time from CT simulation to partial breast radiotherapy.

Measured as the time from the day of CT simulation to the first fraction of PBI for Arm 1 or day of single-fraction PBI for Arm 2.

Local control rates.

Local control measured as the absence of ipsilateral in-breast recurrence, defined as histologic evidence of invasive or in situ breast cancer in the ipsilateral breast.

Quality of life.

Assessed using the Prospective Outcomes and Support Initiative (POSI) for Breast Data questionnaire, administered at baseline, then at 2 weeks, 2 months, 6 months, 12, months, 18 months, and 24 months post-treatment.

Rates of provider-rated toxicities.

Occurrences of adverse events as measured by CTCAE assessed during treatment then at 2 weeks, 2 months, 6 months, 12, months, 18 months, and 24 months post-treatment.

Rates of participant-reported toxicities.

Occurrences of adverse events as measured by PRO-CTCAE assessed during treatment then at 2 weeks, 2 months, 6 months, 12, months, 18 months, and 24 months post-treatment.

Overall Survival (OS).

Time from randomization to death from any cause, or last follow-up, whichever occurs first. [Time Frame: approximately at the end of year 2 (study completion)]

Progression-free survival (PFS).

Time from randomization to disease progression at any site, death, or last follow-up, whichever occurs first. [Time Frame: at 6 weeks, 6 months, 12 months, 18 months, and approximately at the end of 24 months]

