## Exclusion criteria

### Participants are excluded from the study if any of the following criteria apply

History of non-breast malignancies except adequately treated non-melanoma skin cancers, in situ cancers treated by local excision or other cancers curatively treated with no evidence of disease for ≥ 5 years.Uncontrolled concurrent malignant cancer.Seroma not visible.Ipsilateral implanted cardiac device.Prior radiotherapy requiring summation for planning.Inability to meet mandatory planning constraints.Requirement for a radiation boost (as determined by treating investigator).Positive lymph nodes.Positive surgical margins defined as “ink on tumor” (any invasive or DCIS cells on ink).Surgical cavities lacking clear delineation (surgical clips are not required but may assist in target delineation).Known germline BRCA1/2 mutation.Serious medical comorbidities precluding radiotherapy (i.e., connective tissue disorders such as lupus or scleroderma).Pregnant or breastfeeding.

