## Pre-treatment evaluation

History and Physical Examination within eight weeks of study registration (No exceptions to timelines):Including prior cancer therapies, and cancer-specific concomitant medications.Chemotherapy and surgery within twelve weeks of RT start date (No exceptions to timeline).Pregnancy test for people of child-bearing potential within 4 weeks of RT start date (No exceptions to timeline).

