### Follow-up evaluation and assessment of efficacy

After treatment, participants will be followed up after 2 weeks. Clinical follow-up appointments will then be scheduled at 2 months, 6 months, 12 months, 18 months, and 24 months, and may be conducted via telephone or videolink. Follow-up visits requiring a physical exam may still be conducted via telephone/videolink if the physical exam is performed within the specified window by the participant’s Family Practitioner (FP) or General Practitioner in Oncology (GPO), with documentation. Otherwise, the participant must return to the clinic for the physical exam to be performed on-site. At each visit, a medical history will be conducted by the oncologist, and CTCAE toxicities recorded using the adverse events form, as well as ECOG scores. The POSI-Breast questionnaire is to be completed at baseline and on each follow-up visit.

A mammogram will be done beginning 6 months after treatment, then annually thereafter. Cytological or histological confirmation of the ipsilateral and contralateral primary tumor is required, including at the time of recurrence.

There is no planned follow-up at the end of the study. Additional care or follow-up assessments that will be provided to participants after they complete or discontinue the study will involve standard of care treatment for what is normally expected for their condition.

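### CTCAE and PRO-CTCAE start during treatment with no pre-radiation grading, so early toxicity rates will include symptoms left over from recent surgery

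*Protocol article*

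**What the plan says.** Secondary Endpoint(s) gives each instrument its own schedule. POSI is "administered at baseline, then at 2 weeks, 2 months, 6 months" and onward to 24 months. Provider-rated toxicity is defined as "Occurrences of adverse events as measured by CTCAE assessed during treatment then at 2 weeks" and onward to 24 months, and participant-reported toxicity has the same schedule: "Occurrences of adverse events as measured by PRO-CTCAE assessed during treatment then at 2 weeks" and onward to 24 months.

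Follow-up evaluation and assessment of efficacy keeps the distinction: "The POSI-Breast questionnaire is to be completed at baseline and on each follow-up visit". CTCAE is recorded there at visits after treatment, with no baseline mentioned.

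Pre-treatment evaluation asks for a history and physical examination, a pregnancy test and a timing rule, "Chemotherapy and surgery within twelve weeks of RT start date". It lists no graded symptom assessment.

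Methods makes comparison of provider-rated and self-reported toxicity between the arms an aim. Statistical methods reports adverse events as descriptive rates and mentions no baseline.

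**The concern.** Everyone in this trial has had a lumpectomy in the weeks before radiation, and some may also have had chemotherapy in that period. Pain, swelling or skin change at the first toxicity assessment may therefore predate radiation. The endpoint counts occurrences, and the article states no rule that separates a symptom already present from one that is new or worse.

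Two things are at stake. The absolute toxicity rate in each arm, which readers will take as the toxicity of the 1- and 5-fraction regimens, will be too high at the early visits. The comparison between arms will also be less sensitive than 60 participants could make it, and these data are meant to lead into a phase III trial. A pre-radiation grade that was not taken cannot be recovered later.

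**Working it through.** **Reading the schedule.** The article states a starting point for all three instruments: baseline for POSI, during treatment for CTCAE and for PRO-CTCAE. The POSI baseline is stated in two sections; a toxicity baseline is stated in none. The assessment during treatment cannot stand in for one, because radiation has already begun.

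**Inputs for an illustration.** The article gives no toxicity rates and no sample-size formula, so there is no stated figure to reproduce. From the article: 60 participants at 1:1, about 30 per arm. Assumed:
- radiation-caused rates r of 10% and 30% in the two arms;
- a share b of participants, equal in both arms, who still have the symptom from before radiation at the visit in question, with b from 0 to 50%;
- independence of the two causes.

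**Formulas.**
- Crude rate: p = 1 − (1 − b)(1 − r).
- Difference: d = p2 − p1 = (1 − b)(r2 − r1).
- Standard error: SE = sqrt[(p1(1 − p1) + p2(1 − p2))/30].
- Nominal power, two-sided 5%: Φ[(d − 1.96 × sqrt(2m(1 − m)/30))/SE], where m is the mean of p1 and p2. No test of toxicity is planned, so power is only a yardstick.

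| b | Crude rates | d (points) | SE (points) | Nominal power |
|---|---|---|---|---|
| 0 | 10% vs 30% | 20 | 10.0 | 49% |
| 10% | 19% vs 37% | 18 | 11.4 | 34% |
| 20% | 28% vs 44% | 16 | 12.2 | 25% |
| 30% | 37% vs 51% | 14 | 12.7 | 19% |
| 50% | 55% vs 65% | 10 | 12.6 | 12% |

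Worked row, b = 30%: p1 = 1 − 0.7 × 0.9 = 0.37; p2 = 1 − 0.7 × 0.7 = 0.51; SE = sqrt[(0.2331 + 0.2499)/30] = 0.127.

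**Inflation of the absolute rate.** This is b(1 − r). At b = 30% it is 0.3 × 0.9 = 27 points where r = 10%, and 0.3 × 0.7 = 21 points where r = 30%.

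**What a baseline recovers.** If only new onsets are counted over all 30 per arm, the rates at b = 30% are 0.7 × 0.10 = 7% and 0.7 × 0.30 = 21%. The difference is still 14 points, but SE = sqrt[(0.0651 + 0.1659)/30] = 0.088, so d/SE rises from 0.14/0.127 = 1.10 to 0.14/0.088 = 1.60. If radiation also raises the grade in those already symptomatic, counting worsening as well brings the contrast back towards 10% vs 30%, with d/SE = 0.20/0.10 = 2.0. Grades are therefore needed at baseline, not merely presence or absence.

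**The case against.** The strongest reply is that this is a condensed article. The full protocol's visit calendar is not at hand, and the article's schedule text has other gaps: Pre-treatment evaluation leaves out the POSI baseline that two other sections require, and the follow-up section never mentions PRO-CTCAE. It is also normal to define an adverse-event rate from the start of treatment and a quality-of-life score against baseline. So the silence of Pre-treatment evaluation proves little, and the full protocol may schedule a baseline. But Secondary Endpoint(s) is not silent: it names a start for each instrument, and the start differs.

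Second, both arms are post-surgical and randomized 1:1 within centre, so surgical symptoms balance in expectation. That stands: it rules out systematic bias between the arms. It does not help absolute rates or sensitivity. The history and physical examination and the baseline POSI record something about pre-radiation status, but neither is stated to be graded on CTCAE or PRO-CTCAE.

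A reader might infer more than the document supports:

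- **A large bias from chance imbalance.** At 30% prevalence, 1.96 × sqrt(2 × 0.3 × 0.7/30) gives about ±23 points. This is the ordinary sampling error of a difference with 30 per arm, and a confidence interval already reflects it. It is not an added bias, and it would carry over in full only if every symptom persisted.
- **False triggering of the safety committee's limits.** Those limits concern grade 3 and grade 4 or 5 events. Nothing in the article supports an appreciable rate of such events before radiation, and the committee acts at its discretion.
- **An unfair assessment window.** One treatment day against five is inherent in the comparison, and a baseline would not remove it.
- **The exclusion "Seroma not visible" as evidence of symptoms.** The article uses the seroma for target definition and image matching. Visibility on imaging does not show pain or skin change.

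**Conclusion.** The point holds as a modest, inexpensive improvement to secondary endpoints. As written, the schedule has no pre-radiation CTCAE or PRO-CTCAE assessment in a recently operated population. Crude rates will therefore include pre-existing symptoms, chiefly during treatment and at 2 weeks and 2 months. Surgical effects should fade by 12 to 24 months, and the problem with them.

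The consequences are inflated absolute rates and a diluted, noisier difference between arms. It would go too far to say that toxicity cannot be attributed to radiation at all, because the randomized comparison remains unbiased between arms. How large the effect is depends on b, the share with a persisting pre-existing symptom, which the article does not give. Under the assumed 10% vs 30% radiation-caused rates, the 20-point difference shrinks to 18 points at b = 10% and to 10 points at b = 50%. The primary feasibility endpoint and the sample size are untouched. If the full protocol already schedules the baseline, only the wording of the article needs correcting.

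**What to change.** In Secondary Endpoint(s) and in Follow-up evaluation and assessment of efficacy, add CTCAE grading and PRO-CTCAE at the pre-radiation baseline, when POSI is completed. State that toxicity will be reported by arm in two ways: crude rates, and new or worsened events, meaning a maximum post-baseline grade above the baseline grade.

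The cost is one extra questionnaire and one grading form per participant at a time when POSI is already being collected: at most 60 of each. Participants enrolled before the change would have no baseline and would need to be reported as such, so it should be made early.

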## Study design

This is a phase II open-label randomized controlled trial using a 1:1 randomization between two arms (26 Gy in 5 fractions vs. 13 Gy in 1 fraction PBI). Participating institutions will include the six BC Cancer sites. The trial schema is shown in Fig. 1.

**Fig. 1 Fig1:**
[figure not shown]
Trial Schema

## Inclusion criteria

Female participants age 40 or older.Able to provide informed consent.pTis-2 pN0 cM0 breast cancer, with tumor size < 3 cm as per provincial guidelines.Able to complete electronic or paper entry of participant reported outcomes independently or with assistance from caregiver/family/friend/research staff.Eastern Cooperative Oncology Group (ECOG) performance status 0–2.A history and physical examination, including ECOG performance status performed within 8 weeks prior to trial enrollment.Participant is judged able to:Maintain a stable position during therapy.Tolerate immobilization device(s) that may be required to deliver PBI safely.Negative pregnancy test for People of Child-Bearing Potential (POCBP) *within 4 weeks of RT start date*.

## Exclusion criteria

### Participants are excluded from the study if any of the following criteria apply

History of non-breast malignancies except adequately treated non-melanoma skin cancers, in situ cancers treated by local excision or other cancers curatively treated with no evidence of disease for ≥ 5 years.Uncontrolled concurrent malignant cancer.Seroma not visible.Ipsilateral implanted cardiac device.Prior radiotherapy requiring summation for planning.Inability to meet mandatory planning constraints.Requirement for a radiation boost (as determined by treating investigator).Positive lymph nodes.Positive surgical margins defined as “ink on tumor” (any invasive or DCIS cells on ink).Surgical cavities lacking clear delineation (surgical clips are not required but may assist in target delineation).Known germline BRCA1/2 mutation.Serious medical comorbidities precluding radiotherapy (i.e., connective tissue disorders such as lupus or scleroderma).Pregnant or breastfeeding.

